
### Participants

2.3

Inclusion criteria include the following:

1.A total of 60 patients with laryngeal cancer in otolaryngology, Department of Otolaryngology head and Neck Surgery, Affiliated Hospital of Southwest Medical University and the Third People's Hospital of Mianyang city from October 2020 to October 2021 will be selected, aged from18 to 65 years old, regardless of gender;2.Head and neck with bone and soft tissue exposure, or tumor resection after skin grafting cannot repair the wound surface;3.Can fully understand the surgical risks and sign informed consent and ethical consent;

Exclusion criteria include the following:

1.Children, adolescents less than 18 years of age, pregnant women and elderly patients with apparent physical decline;2.Patients with positive iodine allergy test and abnormal renal function;3.Patients with severe temperament diseases who cannot tolerate surgery;4.patients with mental illness who cannot independently sign the informed consent for the operation;

### Interventions

2.4

Patients will be randomly divided into CTA group (n = 20), mimics group (n = 20) and CTA + mimics group (n = 20) according to the numerical table. Patients in the CTA group will receive CTA examination of lower extremities. Patients in mimics group will receive digital technology in the positioning of perforator. Patients in CTA + mimics group will receive CTA + digital technology. All the patients will receive the flap cutting and the flap making; the doctor will determine the perforation branch of the flap with 3-D visual positioning, measure the preoperative indicators intraoperatively and complete the wound repair. Finally, the survival rate, sensitivity, specificity and accuracy of the flap will be measured.

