### Study method

2.2

1.The patients will complete routine preoperative examination to exclude serious systemic diseases, and received enhanced valvular CT scan, so that the doctor could determine the lesion scope and vascular condition in the recipient area;2.The patients will be placed in the supine position, the middle and upper 1/3 of both lower extremities will be radiographically marked, and both lower extremities will be kept naturally straight. Iohexol injection will be injected intravenously from the middle of the elbow. A 256-slice spiral CT (Philips, USA) will be used for continuous CTA scanning from bilateral anterior superior iliac spine to bilateral lower edge of patella. CT scanning parameters will be set as 0.625 mm thickness, 120-140 kV, and 525 mA.3.CTA data preprocessing, search for puncture and define reconstruction area: obtain CTA data in DICOM format and import CTA data into 3-D15.0 software (Materialize, Belgium). After reading the data, 3-D15.0 software automatically creates a 3-D project file and uses the convert function to complete the data conversion and generate the original CTA image. Based on the original cross section, the software automatically reconstructs the continuous sectional images of sagittal plane and coronal plane to form the observation screen of 3 dimensions. The original CTA images will be scanned and observed in three orthogonal sectional views to determine the appropriate location of the perforation of the anterolateral femoral flap. Then, the 3-D reconstruction area will be restricted to 1 side of the supply area with suitable cutting struts with Crop Mask, thus reducing the workload of data segmentation in later period.4.3-D is used to reconstruct bones, blood vessels and skin: a section line is created by using the section line option in the axial window, and the gray value distribution along the line can be obtained. To better observe the transition of soft tissue, cortical bone and cancellous bone, click the option of Start Thresholding and select a certain amount of pixel gray value to segment the bone from anterior superior iliac spine to ipilateral patella. The soft tissue and some discrete voxels are then separated from the bone by means of regional growth. Select the region growth tool from the segmentation toolbar and click on the bone section to add all associated voxels to the new mask. The hip, femur, and patella will be extracted from the shape and outline of the bone at each axis view level using a multi-layer editing tool. The newly added mask will be reconstructed in 3-D to extract the individual bone model. Adjust appropriate thresholds to create a new mask, use a multi-layer editing tool on the axis view to erase irrelevant grayscale values, and retain and extract major blood vessels and perforations. The erased new mask will be reconstructed in 3-D, and the reconstructed plane mask will be duplicated. Use the Edit Mask in 3-D to edit the reconstructed 3-D model. Remove the irrelevant soft tissue with the cover lock tool. Click the erase tool to remove the selected pixels from the Mask. After the 3-D editing function is completed, close the toolbar and carry out 3-D reconstruction on the edited corresponding plane mask, so as to obtain clear blood vessels and perforating branches. Reconstruct the thigh skin, create a new mask, set the segmentation threshold, erase the gray value of irrelevant structure on the axis view, carry out 3-D reconstruction, and use the wrap function to make the reconstructed skin continuously smooth.5.3-D visualization of the model: give bone and blood vessel an opaque and skin transparency High, which allows observation and determination of bone and blood vessel through the skin. To enhance the visual effect, the target perforations and pedicles can be stained to a specific color. Based on the size and shape of the wound in the receiving area and the cutting function in the simulation option, the scope, depth and path of the flap will be simulated along the skin surface to generate a 3-D visual model of the personalized free anterolateral thigh flap.6.Simulated skin flap removal and operation: 3-D will be used to edit and process the reconstructed 3-D model before surgery. After other parts will be hidden, the designed anterolateral thigh flap will be “removed” from the 3-D model together with the vascular pedicle. The simulated data will be transferred to the intraoperative body surface of the patients, and the flap will be surgically removed to verify the accuracy of perforator location, and the anterolateral thigh flap will be transplanted and repaired for head and neck soft tissue defects.7.Routine nursing care after free flap transplantation will be given to promote wound healing. Preoperative and intraoperative measurement data will be processed and analyzed with SPSS20.0 software.

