### Measurement of outcomes

2.5

Vascular anatomy and preoperative design results of the anterolateral thigh flap will be recorded, and intraoperative and preoperative comparisons will be analyzed to explore the clinical efficacy of postoperative patients. After the completion of image digitization, 2 physicians who have been working on the anterolateral thigh flap for more than 4 years read the images in a double-blind way to evaluate whether the location, shape, and scope of the lesion of the patient has invasion or metastasis. When opinions will be different, they read the images together and agreed. Consistency analysis by CTA joint digital technology, digital technology and CTA in the defects of head and neck cancer patients in the orientation of value, when the CTA inspection found perforators preoperative and intraoperative confirmed existence is judged to be (+), when the digital technology can be worn for successful reconstruction is judged to be (+), either in the joint inspection tests to determine the (+), finally to the 3 ways to wear the positioning performance comparison.

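### As described, the mimics arm and the CTA + mimics arm receive the same CTA-based work-up and differ at most in how a positive result is scored

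*Protocol article*

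**What the plan says.** Section 2.4 (Interventions) randomises 60 patients, 20 to each of three groups, and gives each group one sentence:

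- CTA: "Patients in the CTA group will receive CTA examination of lower extremities".
- Mimics: "Patients in mimics group will receive digital technology in the positioning of perforator". No image source is named.
- CTA + mimics: "Patients in CTA + mimics group will receive CTA + digital technology".

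The same section then has the doctor use 3-D visual positioning in all patients.

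Section 2.2 (Study method) describes a single workflow and does not limit any step to an arm. A 256-slice CT "will be used for continuous CTA scanning from bilateral anterior superior iliac spine to bilateral lower edge of patella". The next step is to "obtain CTA data in DICOM format and import CTA data into 3-D15.0 software". Then: "The original CTA images will be scanned and observed in three orthogonal sectional views to determine the appropriate location of the perforation". Bone, vessel and skin models are segmented from that dataset afterwards. The only other CT in the section images the recipient area.

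Section 2.5 (Measurement of outcomes) scores CTA as positive if a perforator is found before surgery and confirmed during it, digital technology as positive if reconstruction succeeds, and the joint method as positive if either test is. It ends with a three-way comparison: "finally to the 3 ways to wear the positioning performance comparison".

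**The concern.** Section 2.4 treats digital technology without CTA as a work-up in its own right. Section 2.2 makes the CTA the raw material of that technology and includes a reading of the CTA sections as part of it. On the description given, a patient in the mimics arm either has no thigh data to reconstruct, or has had the same scan, reading and reconstruction as a patient in the combined arm.

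The stated aim in section 2.1 is to compare survival, sensitivity, specificity and accuracy across the three groups. If the plan is followed as written, a chance difference in flap survival between the two digital arms would be credited to combining the methods. A difference in the diagnostic measures would be credited to the extra imaging when it may only reflect a more generous definition of positive.

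**Working it through.** **1. The plan's own figure.** 3 arms × 20 = 60, which agrees with the text. The article gives no event rate or effect size, so there is no sample-size derivation to reproduce. The question is how the arms are defined.

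**2. The two digital arms side by side.**

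| Element | Mimics | CTA + mimics |
|---|---|---|
| Lower-limb CTA (2.2, step 2) | Needed: the only described source for the model | Yes |
| Original CTA sections read for the perforator (2.2, step 3) | Yes, part of the workflow | Yes |
| Segmentation and 3-D model (2.2, steps 4 and 5) | Yes | Yes |
| Simulated flap transferred to the patient (2.2, step 6) | Yes | Yes |
| 3-D positioning by the doctor (2.4) | Yes | Yes |
| Positive result (2.5) | Reconstruction succeeds | Either CTA or digital is positive |

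Only the last row differs. The two arms hold 20 + 20 = 40 of the 60 patients.

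**3. What the scoring rule can do by itself.** Let s_d and s_c be the sensitivities of the digital and CTA readings. The article gives neither, so values of 0.70 to 0.90 are assumed. On the same images, the either-positive rule gives:

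- independent readings: 1 − (1 − s_d)(1 − s_c)
- nested readings (one method finds everything that the other finds): max(s_d, s_c)

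With s_d = s_c = 0.80, independent readings give 1 − 0.20 × 0.20 = 0.96 and nested readings give 0.80. With s_d = 0.80 and s_c = 0.90, nested readings give 0.90.

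Over the whole assumed range, the combined sensitivity is 0.91 to 0.99 if independent. The gain over digital alone is then s_c(1 − s_d), from 0.70 × 0.10 = 0.07 to 0.90 × 0.30 = 0.27. If nested, the gain runs from 0 to 0.90 − 0.70 = 0.20. None of this needs any difference in what was done to the patient.

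**4. Specificity and accuracy.** An either-positive rule cannot give fewer positives than its digital component. Read literally, a CTA positive requires confirmation at surgery, so the CTA part adds only true positives: accuracy can rise while specificity stays at the digital value. If unconfirmed CTA findings also counted as positive, specificity could fall. For example, with 0.80 for each method and independent readings, it would be 0.80 × 0.80 = 0.64.

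**5. Flap survival.** The scoring rule does not touch it. The described work-ups contain nothing that differs, so a survival difference has no described cause in the addition of CTA.

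**The case against.** The strongest reply is that section 2.5 does distinguish the arms: the joint method has its own rule, so the two arms are not identical on every outcome. That is right, and it limits the point. A reader might infer that the true difference between the two digital arms is zero by construction, so that any significant result between them is a false positive. The documents do not support this for sensitivity, specificity and accuracy, as steps 3 and 4 of the working show. Nor does it follow that CTA against mimics and CTA against the combination estimate the same quantity, because the two digital arms are scored differently. The reply does not rescue the arm, however. Both scores could be computed in every patient who has a reconstruction, without randomising between them.

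A second reply is that this is a condensed article and that rules on who views what may sit in a fuller protocol. They may, and the article does not say that no other image source is possible; it only describes none. But section 2.2 goes down to individual software tools, and the fault is that it conflicts with section 2.4, not that a detail is absent.

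A reader might also take it that three pairwise contrasts are planned. The text announces a comparison of three methods and lists no contrasts, and section 2.6 names only a within-group t-test.

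**Conclusion.** The point holds in this form: as described, the mimics and CTA + mimics arms share one CTA-based work-up and differ at most in the scoring rule. A third of the sample (20 of 60) is assigned to an arm whose separate existence the article does not support. A survival difference between the two digital arms could not be attributed to adding CTA. A difference in the diagnostic measures could be produced by scoring alone: on assumed sensitivities of 0.70 to 0.90, a gain of 0 to 0.27 in sensitivity, depending on how far the two readings overlap.

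The conclusion rests on the CTA being the only thigh image source described and on section 2.2 applying to every arm. It would change if another document restricted what the positioning doctor sees in the mimics arm. The sensitivities are illustrative and set the size of the scoring effect only; the conflict between the sections does not depend on them.

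**What to change.** Reconcile sections 2.2, 2.4 and 2.5 in one of two ways.

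1. **Keep three arms and define them by information.** State what the positioning doctor in the mimics arm does not see (for example, the 3-D model only, without the CTA sections) and what the combined arm adds. Someone else would then have to carry out the CTA reading that section 2.2 places before reconstruction, and the text should say so.
2. **Merge the two digital arms.** Treat them as one group with CTA plus reconstruction, score every patient in it by one common rule, compare it with a CTA arm read without 3-D reconstruction, and withdraw the claim about mimics alone against the combination. This also requires removing the conflict with the 3-D visual positioning that section 2.4 gives to all patients; otherwise the CTA arm is not a reconstruction-free comparator.

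If patients are already allocated 20/20/20 and both conditions of the second option are met, the comparison becomes 40 against 20. With equal variance per patient, its standard error is √[(1/40 + 1/20)/(1/20 + 1/20)] = √(0.075/0.100) = 0.866 times that of 20 against 20. Without those conditions, the pooling would mix two definitions of positive and could compare digital with digital.

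The cost is an amendment to the arm definitions and, under the second option, the loss of a separate statement about mimics alone. No extra patients or scans are needed.

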**Methods/Design::**

A total of 60 patients with laryngeal cancer in otolaryngology, Department of Otolaryngology Head and Neck Surgery, Affiliated Hospital of Southwest Medical University and the Third People's Hospital of Mianyang city from October 2020 to October 2021 will be selected and randomly divided into CT angiogram (CTA) group (n=20), mimics group (n = 20) and CTA + mimics group (n = 20) according to the numerical table. Patients in the CTA group will receive CTA examination of lower extremities. Patients in mimics group will receive digital technology in the positioning of perforator. Patients in CTA + mimics group will receive CTA + digital technology. All the patients will receive the flap cutting and the flap making; the doctor will determine the perforation branch of the flap with 3-D visual positioning, measure the preoperative indicators intraoperatively and complete the wound repair. Finally, the survival rate, sensitivity, specificity and accuracy of the flap will be measured.

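### The arm definitions and the all-patient surgical sentence conflict on whether CTA-arm patients are operated on from a 3-D plan; read literally, flap survival cannot show what digital technology adds to CTA

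*Protocol article*

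**What the plan says.** Section 2.4 (Interventions) randomises 60 patients to three arms of 20 and defines each arm by its localisation method:

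- CTA arm: "Patients in the CTA group will receive CTA examination of lower extremities".
- Mimics arm: "Patients in mimics group will receive digital technology in the positioning of perforator".
- Combined arm: "Patients in CTA + mimics group will receive CTA + digital technology".

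The following sentence opens with all patients, covers the cutting and making of the flap, and continues: "the doctor will determine the perforation branch of the flap with 3-D visual positioning". The abstract (Methods/Design) carries the same sentence: "All the patients will receive the flap cutting and the flap making; the doctor will determine the perforation branch of the flap with 3-D visual".

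Section 2.2 (Study method) sets out seven steps. They include a lower-limb CTA scan, import of the CTA data into the 3-D software, reconstruction and simulated flap harvest. Step 6 then says: "The simulated data will be transferred to the intraoperative body surface of the patients, and the flap will be surgically removed". No step is assigned to an arm or withheld from one.

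Section 2.1 makes the three-arm comparison of flap survival, sensitivity, specificity and accuracy the aim. Section 2.5 scores positivity by method. A CTA finding counts when the perforator is seen before surgery and confirmed during it. A digital finding counts when reconstruction succeeds. The joint method is positive if either one is.

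**The concern.** By their definitions, the CTA and CTA + mimics arms differ only in digital technology, so they are the pair that isolates what it adds to CTA. If the surgeon in the CTA arm also locates the perforator on the 3-D model, the two arms receive the same guidance at the operation. Their flap survival would then be expected to agree whatever the true benefit, and a finding of no difference could be misread as showing that digital technology adds nothing. A site that follows the text has no instruction preventing this, and analysis cannot restore a contrast that was never delivered.

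**Working it through.** The article gives no figure to reproduce here. The check is what each arm receives under each part of the text.

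**Step 1. Exposure to 3-D positioning at surgery** (20 patients per arm, section 2.4)

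| Arm | By the arm definitions | By the all-patient sentence, read literally |
|---|---|---|
| CTA | 0/20 | 20/20 |
| Mimics | 20/20 | 20/20 |
| CTA + mimics | 20/20 | 20/20 |

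Contrast in 3-D exposure, CTA + mimics minus CTA:

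- arm definitions: 20/20 − 0/20 = 100 percentage points
- literal reading: 20/20 − 20/20 = 0

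Both columns come from the same paragraph, and they cannot both describe the trial.

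**Step 2. Does another section settle it?**

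- The abstract repeats both the arm definitions and the all-patient sentence, and so repeats the conflict.
- Section 2.2 describes one continuous route and is silent on arms. Step 3 already brings the CTA data into the 3-D software and looks for the perforator there in three orthogonal views. Step 6 takes the simulated plan to the patient.
- No section says that CTA-arm patients are operated on without the 3-D model.

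**Step 3. Consequence for each outcome under the literal reading**

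- *Flap survival.* It depends on the operation. With 3-D exposure equal in the CTA and CTA + mimics arms, no expected difference can be attributed to digital technology.
- *Sensitivity, specificity and accuracy.* Section 2.5 scores calls by method, so a comparison of methods does not disappear because the surgeon later uses a 3-D plan. It does depend on the CTA call being made before the 3-D output is seen, which the article does not state. A CTA positive also needs intraoperative confirmation, and under the literal reading the surgeon seeks that confirmation with the model as a guide.

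**The case against.** The strongest reply is that the sentence is loosely written and nothing more is planned. The reference to all patients governs the cutting and making of the flap. After the semicolon the subject becomes the doctor, and the three preceding sentences have just given arm-specific methods, which could be taken to control the general one. Section 2.2 presents the full technique once, before the arms are introduced. Its steps 3 to 5 do not mention patients, so its silence on arms in a condensed article is weak evidence that every arm gets every step.

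This reply stands in part. It shows that the authors may have meant 3-D positioning only for the digital arms. It does not remove the conflict, because nothing in the article states that restriction. Condensation does not explain it either: the problem is a positive statement, made twice, that disagrees with the arm definitions beside it.

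A reader might infer more: that contamination is the settled design, that the CTA arm is useless as a comparator for every outcome, and that the study's central conclusion fails with it. The document does not support this. The intended use is ambiguous. Three of the four named outcomes rest on calls that section 2.5 scores by method. The Discussion speaks only of CTA combined with digital technology and names no CTA-alone comparator, so it cannot be said to rely on that contrast.

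**Conclusion.** The point holds as an internal contradiction in the abstract and section 2.4, left unresolved by section 2.2. Followed literally, all 20 CTA-arm patients receive 3-D-guided surgery, the CTA versus CTA + mimics contrast in that guidance is zero, and flap survival cannot show what digital technology adds to CTA. The localisation measures are at risk, through the order in which images are read and through model-guided confirmation, but they are not necessarily lost.

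This conclusion assumes that sites act on the text as written and that digital technology affects survival through its use at surgery. If only some CTA-arm patients were positioned with the model, the survival contrast would be weakened and not removed. The document gives neither that proportion nor an expected effect, so no numerical loss can be stated beyond the exposure counts. The wording needs correcting before the trial relies on it, because it determines what the randomised arms contain.

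**What to change.** Reconcile the abstract and sections 2.2 and 2.4 by stating which steps apply to which arm. This must include step 3 of section 2.2, because the 3-D software comes into use there and not only at the later modelling steps. That step also builds the 3-D model from CTA data, so the same rewording should say what the mimics arm receives. Which steps belong in which arm is for the sponsor and investigators to decide.

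In either case, record each allocated method's perforator call before surgery and before any other method's output is seen.

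If every arm is in fact operated on from the 3-D plan, say so. Flap survival should then not be interpreted as a between-arm effect of the localisation method, and the comparison should be limited to the pre-recorded localisation calls.

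Cost: wording changes in those places and one pre-surgery record per patient. In the second case the trial also gives up flap survival as comparative evidence.

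### The intraoperative reference is taken with the 3-D plan already on the patient, and section 2.4 blurs the preoperative and intraoperative measurements, so agreement is expected to be biased upward by an unknown amount

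*Protocol article*

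**What the plan says.** Four places in the protocol article bear on this point.

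- **Interventions (2.4)**, for every patient: "the doctor will determine the perforation branch of the flap with 3-D visual positioning, measure the preoperative indicators intraoperatively and complete the wound repair".
- **Study method (2.2), step 6**: "The simulated data will be transferred to the intraoperative body surface of the patients", after which "the flap will be surgically removed to verify the accuracy of perforator location". Step 7 then refers to preoperative and intraoperative measurements as two kinds of data.
- **Measurement of outcomes (2.5), blinding**: two physicians "read the images in a double-blind way to evaluate whether the location, shape, and scope of the lesion of the patient has invasion or metastasis". No other blinding is described. The same section says that preoperative design results are recorded and compared with intraoperative ones.
- **Measurement of outcomes (2.5), scoring**: CTA is positive "when the CTA inspection found perforators preoperative and intraoperative confirmed existence is judged to be" (+). The digital method is positive "when the digital technology can be worn for successful reconstruction is judged to be" (+).

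Sections 2.1 and 2.4 name sensitivity, specificity and accuracy among the outcomes, alongside flap survival.

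**The concern.** When an imaging method is judged against a surgical finding, the finding should not depend on what the imaging showed. Here the plan is in the operative field while the reference is obtained. Two mechanisms follow, both pushing apparent performance up:

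1. Someone who knows the predicted position will tend to resolve borderline cases as agreement.
2. If exploration follows the plan, a perforator that the imaging missed may never be exposed, and so is never counted as a miss.

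The wording of 2.4 adds a further difficulty. Read literally, an indicator called preoperative is measured during surgery. A value taken then is not independent of the finding it is compared with. At stake is whether the reported agreement describes the imaging or partly describes the procedure used to check it. A larger sample would not reduce such a bias.

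**Working it through.** **Step 1. Who locates, who verifies, who is blinded**

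| Element | Section | What the text supports |
|---|---|---|
| Locating the perforator | 2.4 | The doctor, using 3-D positioning, in all patients |
| Plan visible at surgery | 2.2, step 6 | Yes, transferred to the body surface |
| Verifying step | 2.2, step 6 | Raising the flap; the person who measures is not named |
| Measuring in theatre | 2.4 | The doctor, the same grammatical subject as for locating |
| Blinding | 2.5 | Two image readers, assessing the lesion |

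No row shows the theatre measurement being made without knowledge of the plan.

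**Step 2. Are the two measurements kept apart?** In 2.2 (step 7) and 2.5, yes: preoperative and intraoperative results are distinct and are compared. In 2.4, no: one phrase merges them. The sections need to be reconciled.

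**Step 3. Which measures are exposed?** Those that rest on intraoperative confirmation. The CTA rule names it explicitly. The digital rule names reconstruction only. The general preoperative-to-intraoperative comparison in 2.5 is exposed whichever method is used.

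**Step 4. Direction and possible scale.** The article states no accuracy or agreement rate, so there is no figure of its own to reproduce. The inputs below are assumptions, chosen only to show direction.

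*Lenient concordance.* Let A be true agreement and f the share of discordant findings called concordant. Observed agreement = A + f(1 − A). For A = 0.80 and f = 0.25: 0.80 + 0.25 × 0.20 = 0.85.

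| True A | f = 10% | f = 25% | f = 50% |
|---|---|---|---|
| 0.70 | 0.730 | 0.775 | 0.850 |
| 0.80 | 0.820 | 0.850 | 0.900 |
| 0.90 | 0.910 | 0.925 | 0.950 |

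*Incomplete exposure.* Let Se be true sensitivity and v the share of imaging-missed perforators that surgery still exposes and records. Observed sensitivity = Se / (Se + v(1 − Se)). For Se = 0.80 and v = 0.50: 0.80 / (0.80 + 0.50 × 0.20) = 0.80 / 0.90 = 0.889.

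| True Se | v = 75% | v = 50% | v = 25% |
|---|---|---|---|
| 0.70 | 0.757 | 0.824 | 0.903 |
| 0.80 | 0.842 | 0.889 | 0.941 |
| 0.90 | 0.923 | 0.947 | 0.973 |

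Every entry lies above the true value. The direction therefore does not depend on the inputs, provided f is above 0 or v below 1. The size depends on them entirely.

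**The case against.** The strongest reply is that 2.4 is loose English. Since 2.5 has preoperative design results recorded, and 2.2 simulates the flap before surgery, the phrase most plausibly means that indicators already measured on the images are measured again in theatre. This is a fair reading, and it rules out a stronger claim that a reader might infer: that nothing fixes the preoperative value before the vessel is seen. The value exists beforehand. What remains is that 2.4 says otherwise and no section puts the value beyond revision before incision.

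A reader might also infer that the bias favours the digital arms, or that the surgeon knows the arm from the plan on the skin. The text supports neither. Section 2.4 applies 3-D positioning to all patients, so as written the overlay is common to the arms. The digital rule in 2.5 names no intraoperative confirmation, so a lenient theatre judgement could raise the CTA call without touching the digital one. Two favourable reclassifications among 20 digital patients and none among 20 CTA patients would make a gap of 2/20 = 10 points, but that split would be arbitrary.

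The same-person point rests on grammar in 2.4. The doctor may be a generic term, and 2.2 names no measurer. This stands as a caution, but the core point survives it: anyone measuring in that field works with the plan in view. The blinded reading in 2.5 is no rebuttal, since even if it were meant to include perforators it would cover image readers and not the theatre finding.

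Finally, forms and assessor details are commonly left to a full protocol. I agree, and their absence is not the point. The point is the verification procedure that the article does describe.

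**Conclusion.** The concern holds in a limited form. As described, the surgical reference is obtained with the 3-D plan known and displayed, the stated blinding does not cover that step, and 2.4 blurs two measurements that 2.2 and 2.5 keep separate. Agreement, and sensitivity and accuracy where they rest on intraoperative confirmation, are expected to be biased upward. The documents do not allow the size to be estimated. The figures above rest wholly on assumed values of A, Se, f and v, and the second mechanism also assumes that exploration follows the plan, which the article does not spell out. No claim is made about which arm would gain, about specificity, or about flap survival. This merits a cheap correction; it does not invalidate the design.

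**What to change.** 1. **Reword 2.4** so that the preoperative indicators are measured on the images, recorded and locked before incision, and the same indicators are measured separately in theatre. Align 2.2 (steps 6 and 7) and 2.5 with that wording.
2. **Record the intraoperative perforator position from fixed bony landmarks**, not as a match to the transferred mark. The anterior superior iliac spine and the patella already bound the scan range in 2.2.
3. **Derive concordance afterwards** from the two sets of values, by one prespecified rule applied identically in all three arms. The document gives no basis for a particular tolerance, so the investigators must set and justify it before data are collected.
4. **State the limitation** that the surgeon still sees the plan. These changes make the two measurements more independent; they do not mask the operator.

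The cost, in my judgement, is a few minutes of extra recording per case, with no added procedure, no added staff and no change to treatment. The change should be made before data collection, because unlocked values cannot be made independent afterwards.
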